## LIST OF ABBREVIATIONS AND RELEVANT DEFINITIONS

|                             |                                                                                                                                                                                                                                                                                                                                                  |
|-----------------------------|--------------------------------------------------------------------------------------------------------------------------------------------------------------------------------------------------------------------------------------------------------------------------------------------------------------------------------------------------|
| F-FDG   | 2-[F-18]-fluoro-2-deoxy-D-glucose                                                                                                                                                                                                                                                                                                         |
| Ga-PSMA | Gallium-68-Prostate Specific Membrane Antigen                                                                                                                                                                                                                                                                                             |
| ABR                  | ABR form, General Assessment and Registration form, is the application form that is required for submission to the accredited Ethics Committee (In Dutch, ABR = Algemene Beoordeling en Registratie)                                                                                                                                      |
| AE                   | Adverse Event                                                                                                                                                                                                                                                                                                                             |
| AR                   | Adverse Reaction                                                                                                                                                                                                                                                                                                                          |
| CA                   | Competent Authority                                                                                                                                                                                                                                                                                                                       |
| CT                   | Computed Tomography                                                                                                                                                                                                                                                                                                                       |
| CCMO                 | Central Committee on Research Involving Human Subjects; in Dutch: Centrale Commissie Mensgebonden Onderzoek                                                                                                                                                                                                                               |
| CV                   | Curriculum Vitae                                                                                                                                                                                                                                                                                                                          |
| DSMB                 | Data Safety Monitoring Board                                                                                                                                                                                                                                                                                                              |
| dPET/CT              | Dynamic PET/CT                                                                                                                                                                                                                                                                                                                            |
| EU                   | European Union                                                                                                                                                                                                                                                                                                                            |
| GCP                  | Good Clinical Practice                                                                                                                                                                                                                                                                                                                    |
| IB                   | Investigator's Brochure                                                                                                                                                                                                                                                                                                                   |
| IC                   | Informed Consent                                                                                                                                                                                                                                                                                                                          |
| METC                 | Medical Research Ethics Committee (MREC); in Dutch: Medisch Ethische Toetsing Commissie (METC)                                                                                                                                                                                                                                            |
| NKI-AVL              | Netherlands Cancer Institute – Antoni van Leeuwenhoek                                                                                                                                                                                                                                                                                     |
| PCa                  | Prostate Cancer                                                                                                                                                                                                                                                                                                                           |
| PET                  | Positron Emission Tomography                                                                                                                                                                                                                                                                                                              |
| PSMA                 | Prostate Specific Membrane Antigen                                                                                                                                                                                                                                                                                                        |
| Sponsor              | The sponsor is the party that commissions the organisation or performance of the research, for example a pharmaceutical company, academic hospital, scientific organisation or investigator. A party that provides funding for a study but does not commission it is not regarded as the sponsor, but referred to as a subsidising party. |
| SUSAR                | Suspected Unexpected Serious Adverse Reaction                                                                                                                                                                                                                                                                                             |
| Wbp                  | Personal Data Protection Act (in Dutch: Wet Bescherming Persoonsgegevens)                                                                                                                                                                                                                                                                 |
| WMO                  | Medical Research Involving Human Subjects Act (in Dutch: Wet Medisch-wetenschappelijk Onderzoek met Mensen)                                                                                                                                                                                                                               |

## SUMMARY

**Rationale:** Prostate cancer is the third most common cancer in Europe and is still the leading cancer among men in the Netherlands with over 13,000 men diagnosed each year. Ga-Prostate Specific Membrane Antigen (Ga-PSMA) is an emerging imaging agent that already has been widely proven as a highly effective agent for restaging PCa cells, but also holds enormous potential for initial staging and image guided surgery. During surgery, Ga-PSMA can potentially be used for the assessment of resection margins based on Cerenkov Light emission. The interval between initial staging and subsequent prostatectomy surgery, however, ranges from 4 to 6 weeks. Since little is known about the PSMA expression over time without intervention, a study on this is required. If PSMA expression is equal between both scans, the inclusion and dose determination for image guided surgery can be based on the clinical Ga-PSMA PET/CT scan. In order to validate this, two PET scans will be performed in a test-retest setting in primary prostate cancer patients. Dynamic imaging will be performed in order to get insight into the optimal scan time. Subsequently this will be used also to establish the ideal timing of surgery after injection.

**Objective:** The objective of this study is to obtain preliminary data on variability in PSMA expression by comparing the tracer uptake on conventional clinical Ga-PSMA PET/CT with an additional Ga-PSMA PET/CT (4 weeks later) within primary prostate cancer patients. Dynamic imaging will be performed in order to get insight into the most ideal scan time.

**Study design:** This is a prospective observational study.

**Study population:** This study will include 30 primary prostate cancer patients.

**Intervention (if applicable):** Not applicable.

**Main study parameters/endpoints:** The main study endpoint is to evaluate the PSMA expression variation at 4 week intervals. The secondary endpoint is to determine the optimal time between Ga-PSMA injection and prostate surgery for future image-guided surgery.

**Nature and extent of the burden and risks associated with participation, benefit and group relatedness:** The patients included in this study have an additional radiation exposure of 6.3mSv, since they need to undergo an additional Ga-PSMA PET/CT-scan. This is 9.3mSv for the patients with the dynamic PET/CT-scan.

## 1. INTRODUCTION AND RATIONALE

Prostate cancer (PCa) is the second most common cancer amongst men in the world, recorded in 2012. And the most common among men in the Netherlands.

Positron Emission Tomography (PET) / Computed Tomography (CT) scanners are used to detect malignancies throughout the body. For PCa 68-Gallium Prostate Specific Membrane Antigen (Ga-PSMA) is a tumour specific radiopharmaceutical. Since PSMA is a membrane-bound enzyme which is overexpressed in PCa cells in comparison to benign prostatic tissue (approximately 100- to 1000-fold more PSMA expression). This makes Ga-PSMA an emerging imaging agent that already has been widely proven as a highly effective detector of PCa cells, and therefore, holds enormous potential for medical imaging. In the last years, Ga-labelled tracers are increasingly used for PET-imaging due to the in-house availability of GMP-approved Ga generators. Nowadays, Ga-based tracers are commonly used within Europe for targeted diagnostic imaging in specific tumour types like prostate cancer

Three large-scale European studies reported detection rates for recurrent prostate cancer above 95%. Afshar-Oromieh et al. showed positive and negative predictive values of, respectively, 91.4% and 100% in 319 prostate cancer patients. Eiber et al. found a 96.8% detection rate in 248 patients with biochemical recurrence after radical prostatectomy using PET/CT. Maurer et al. reported a 95.2% accuracy in 130 patients with intermediate to high-risk prostate cancer. The same study found that Ga-PSMA was significantly superior to conventional anatomical imaging ( $p < 0.001$ ). Rahbar et al. found a very high agreement between Ga-PSMA and histopathology. Due to the superiority of Ga-PSMA over other imaging approaches, Ga-PSMA is fast emerging as the gold standard for *in vivo* detection of prostate cancer. The PET signal depends on the number of cells expressing the membrane enzyme, PSMA expression per cell and the imaging system resolution. In general the tumour uptake correlates with the absolute cell surface PSMA expression.

Ga-PSMA is an emerging imaging agent that already has been widely proven as a highly effective agent for restaging PCa cells, but also holds enormous potential for initial staging and image guided surgery. During surgery, Ga-PSMA can be probably be used of assessment of the resection margins based on Cerenkov Light emission. This is part of study granted by KWF (grant number 15175). The interval between initial staging and its application in surgical setting, however, ranges from 4 to 6 weeks. Since little is known about the PSMA expression over time without intervention, a study on this is required to verify this. If PSMA expression is equal between both scans, the inclusion and dose determination can be based on the clinical PET/CT scan. In order to validate this, two PET scans will be performed in a test-retest setting in primary prostate patients. Dynamic imaging will be performed in order to get insight into the most ideal scan time. Subsequently this will be used also to establish the ideal timing of surgery after injection.

## 2. OBJECTIVES

### Primary Objective:

To obtain preliminary data on variability in PSMA expression by comparing prostate uptake on standard clinical  $^{68}\text{Ga}$ -PSMA PET/CT with  $^{68}\text{Ga}$ -PSMA PET/CT performed 4 weeks later.

### Secondary Objective:

Dynamic imaging will be performed in order to get insight into the most ideal scan time.

## 3. STUDY DESIGN

This is a single centre prospective observation study without randomisation.

### 3.1 PSMA expression over time

The aim is to obtain preliminary data on variability in PSMA receptor expression by comparing prostate uptake on standard clinical  $^{68}\text{Ga}$ -PSMA PET/CT with additional  $^{68}\text{Ga}$ -PSMA PSMA PET/CT in a 4 week interval.

Primary prostate cancer patients will be included using routine MRI examinations. Based on protocol, a  $^{68}\text{Ga}$ -PSMA PET/CT scan will be advised on high risk prostate cancer patients (cT3, Gleason score >7, PSA >20 ng/mL). These patients will be asked to participate in the study. If they agree to participate, the patients will undergo another  $^{68}\text{Ga}$ -PSMA PET/CT scan within 4 weeks after the routine diagnostic scan. The protocol for the second scan is equal to the standard diagnostic  $^{68}\text{Ga}$ -PSMA PET/CT scan. The PET scan will be acquired at approximately 45 minutes after administration of ~100MBq  $^{68}\text{Ga}$ -PSMA.

In the 5 patients, a dynamic PET/CT-scan (dPET/CT) is acquired up to 40 minutes after administration of the radiopharmaceutical. The dPET/CT scan is performed at one bed position with the prostate in the central field-of-view (FOV). The low-dose CT scan of the same region is made before tracer injection, for attenuation correction and anatomic localization. dPET/CT imaging is started immediately after intravenous injection of 100 MBq  $^{68}\text{Ga}$ -PSMA.

The static PET/CT acquisition is performed directly after the dynamic series. Between the dynamic and static acquisition, the patient is requested to void.

**Table 1.** Division of subgroups in the clinical phase.

| Phase                   | Subgroup   | Administration for PET (MBq) |
|-------------------------|------------|------------------------------|
| 1a – dynamic and static | I. n = 5   | 100                          |
| 1b – static             | II. n = 25 | 100                          |

## 4. STUDY POPULATION

### 4.1 Population (base)

30 patients with a primary prostate carcinoma will be included for this study. These patients should be eligible for a standard  $^{68}\text{Ga}$ -PSMA -PET/CT-scan, according to clinical protocol. The patients will be recruited from the Urology department of the Antoni van Leeuwenhoek (AvL) hospital in Amsterdam. Initially, 30 patients, of whom 5 patients will undergo both dynamic and static PET/CT imaging, will be included. If a patient does not show PSMA expression on the first PET scan, this patient is excluded for the second scan, and will be replaced by another patient.

### 4.2 Inclusion criteria

A subject must meet all of the following criteria:

- Proven primary prostate carcinoma
- >18 years
- Good knowledge of Dutch language
- Written informed consent
- Underwent a pelvic MRI-scan
- Eligible for  $^{68}\text{Ga}$ -PSMA PET/CT
- Lesion bigger than 10mm, to minimize partial volume effects

### 4.3 Exclusion criteria

A potential subject who meets any of the following criteria will be excluded from participation in this study:

- Contraindications for a PET/CT scan.
- Therapy scheduled between scans
- No PSMA expression on first PET scan

### 4.4 Sample size calculation

Paired measurements of 30 patients will provide 80% to show the equivalence of the two tests (4 weeks before surgery and 1 day before surgery) assuming that accepted boundary of equivalence is symmetric and equals 30%. A variation more than 30% is considered clinically relevant, according to PERCIST criteria. We expect that the second measurement will be different from the first measurement by no more than 10%. Coefficient of variation is assumed to be between 0.6 and 0.7 and within-subject correlation is assumed to be 0.8-0.85.

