## **7. STATISTICAL ANALYSIS**

### **7.1 Primary study parameter(s)**

All the data will be collected and quantitatively analysed within the NKI-AvL. The number and location of lesions are determined by a nuclear medicine physician. The absolute uptake in Bq/mL of the voxels will be determined using standard software (Osirix MD viewer). A paired t-test is used to compare uptake values of  $^{68}\text{Ga}$ -PSMA of the first and the second scan.

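### Section 4.4 gives one 80% power figure without a significance level or a reference for the 30% margin; if the first-scan mean is estimated from the same 30 patients, power at a full +10% shift is about 62–83%

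*Protocol*

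**What the plan says.** Protocol section 4.4 states that "Paired measurements of 30 patients will provide 80% to show the equivalence of the two tests". The margin is introduced by "assuming that accepted boundary of equivalence is symmetric and equals 30" per cent. The true shift is bounded without a direction: "We expect that the second measurement will be different from the first measurement by no more than 10" per cent. The spread enters as "Coefficient of variation is assumed to be between 0.6 and 0.7 and within-subject correlation is assumed to be 0.8-0.85". The section gives no significance level, formula or software. It also does not say whether the 30% applies to a difference, a ratio or a log-ratio, or to which mean it refers.

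Section 7.1 sets the measurement scale: "The absolute uptake in Bq/mL of the voxels will be determined using standard software". For the analysis it says "A paired t-test is used to compare uptake values of" the tracer on the two scans. It names no equivalence procedure.

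**The concern.** Margin, shift and spread in 4.4 are all relative to a mean, but 7.1 analyses uptake in Bq/mL. On that scale a 30% margin needs a reference mean. None is supplied from outside, so it has to come from the 30 patients themselves. With a CV of 0.6–0.7 its standard error is 0.6/√30 = 11.0% to 0.7/√30 = 12.8% of the mean. That is not small beside the 20 percentage points between a 10% shift and the 30% limit.

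The result matters for later work. According to the Summary and section 1, if uptake is the same on both scans, the clinical scan can serve for inclusion and dose determination in image-guided surgery. If true equivalence is missed more often than the stated 20%, a non-conclusive result may be misread as instability of PSMA uptake. If the uncertainty of the mean is simply ignored in the analysis, equivalence may be declared falsely too often.

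**Working it through.** **Inputs.** From 4.4: n = 30 pairs, margin 0.30, shift up to 0.10, CV 0.6–0.7, correlation r 0.80–0.85. Withdrawn patients are replaced (6.4), so no inflation for dropout is needed. Assumption, because 4.4 gives no level: two one-sided 5% tests. All quantities are in units of the first-scan mean.

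**Step 1: reproduce the 80%.** With a fixed margin and equal SDs, SD of the difference = CV × √(2(1 − r)), and n = (1.645 + 0.842)² × SD² / (0.30 − 0.10)².

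At CV 0.7 and r 0.8, SD² = 0.49 × 0.4 = 0.196, so n = 6.185 × 0.196 / 0.04 = 30.3. Power with 30 pairs is 79.6% (normal) or 77.9% (t). Over the four corners it is 80–95% (normal) or 78–95% (t). On this reading 80% is the floor of the stated range.

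Other settings also lead to about 80%. At one-sided 2.5%, (1.960 + 0.842)² = 7.85:
- CV 0.6, r 0.80: n = 7.85 × 0.144 / 0.04 = 28.3
- CV 0.7, r 0.85: n = 7.85 × 0.147 / 0.04 = 28.8

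The stated figure therefore does not identify the method.

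**Step 2: let the mean be estimated.** Equivalence with ratio limits 0.70–1.30 is tested by paired t-tests on (scan 2 − 1.3 × scan 1) and (scan 2 − 0.7 × scan 1). This corresponds to a Fieller interval for the ratio of means. At +10% the first contrast decides. Its mean is 1.1 − 1.3 = −0.20. With a common CV the second-scan SD is 1.1 × CV, so its variance is CV² × (1.21 + 1.69 − 2.86r).

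At CV 0.7 and r 0.8 the variance is 0.49 × 0.612 = 0.300 and the standard error is √(0.300/30) = 0.100. Then 0.20/0.100 = 2.0 against t = 1.70, and Φ(2.0 − 1.70) ≈ 62%. Simulation gives the same value.

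| CV, r | Fixed margin, equal SDs (t), +10% | Ratio of means, +10%, normal: common CV / equal SDs | Ratio of means, +10%, lognormal, common CV |
|---|---|---|---|
| 0.7, 0.80 | 78% | 62% / 62% | 67% |
| 0.7, 0.85 | 87% | 72% / 71% | 78% |
| 0.6, 0.80 | 88% | 74% / 74% | 78% |
| 0.6, 0.85 | 95% | 83% / 82% | 87% |

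With lognormal data and equal SDs the best corner reaches 88%. With normal data about 95–97% of the stated CV-by-correlation rectangle lies below 80% at +10%. The number of pairs that gives 80% at +10% runs from 28–29 (best corner) to 48 (worst corner).

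**Step 3: the other shifts (normal data, same test).** At −10% power is 87–98% with a common CV and about 80–95% with equal SDs. At no shift it is 88–99%.

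**Step 4: log-ratio test, limits 0.70–1.30.** No reference mean is needed. With a common CV and the stated correlation on the raw scale, the variance of the log-ratio is 2[ln(1 + CV²) − ln(1 + r·CV²)].

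At CV 0.7 and r 0.8 this is 2(0.399 − 0.331) = 0.136, with standard error 0.067. ln(1.3/1.1) = 0.167, and 0.167/0.067 ≈ 2.48, so power is Φ(2.48 − 1.70) ≈ 78%. Over the corners at +10% the range is 78–93%. It is 72–90% if the stated correlation is taken on the log scale, and about 66–87% with equal SDs. At −10% the distance to the limit is larger, ln(0.9/0.7) = 0.251, and power is higher.

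**Step 5: the shortcut.** Suppose the confidence interval of the raw difference is compared with 0.30 times the observed mean. At a true +30% this declares equivalence in about 5–10% of trials, depending on the SD and distribution assumptions, against a nominal 5%. The contrasts in step 2 stay at or below about 5%.

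**The case against.** The strongest reply is that the protocol's figure is not an arithmetic error. On its own inputs a standard fixed-margin paired equivalence test gives 80% as the floor of the range. Writing margin and SD relative to an assumed mean is ordinary planning practice. That stands, and a reader who inferred that 4.4 is miscalculated would go further than the text allows. Nor does any passage say that the mean was taken as known. This is inferred from the reproduction, and the one-sided 2.5% settings in step 1 show that it is not the only route to 80%.

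Second, 62–83% belongs to a test that the protocol does not name, and to the unfavourable end of an undirected bound. That also stands. A reader might conclude that the study is underpowered in general or needs 48 pairs. The documents do not support this: at −10% or no shift power is about 80% or more, and 48 pairs apply only to the worst corner at the full +10%. But 4.4 allows 10% in either direction, so the claim has to hold at +10% as well.

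Third, the inflated false-equivalence rate applies only if the observed mean is used as if it were exact, and the protocol does not say that it will be. It is a risk to exclude, not a planned procedure.

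Finally, level and test statistic could be left to a statistical analysis plan, and the study aims only at preliminary data. The power figure, however, is asserted in the protocol itself and cannot be interpreted without the level, scale and reference.

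**Conclusion.** The point holds in a limited form. Section 4.4 states a single power figure without the level and the margin reference that would define it. At the corner that reproduces 30 pairs (CV 0.7, r 0.8), every analysis checked that needs no externally known mean has less than 80% power at +10%: 62–78% at one-sided 5%. For the ratio-of-means test, the chance of missing true equivalence there is up to 100 − 62 = 38%, not 20%.

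This rests on the assumed one-sided 5% level, ratio limits of 0.70–1.30 around the first-scan mean, and a true shift of the full +10%. At one-sided 2.5% the ratio-of-means range would fall to about 48–73%. The difference between common CV and equal SDs hardly affects the ratio test at +10%, but it matters for the log-ratio test. The defect lies in how the power is specified and reported. It does not show that 30 patients are too few for the stated aim.

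**What to change.** Keep 30 patients and restate section 4.4:

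- Give the level, for example two one-sided 5% tests with a 90% confidence interval.
- Say that the margin is 30% of the first-scan mean, that is, ratio limits of 0.70–1.30.
- Replace the single 80% with the power range for the chosen scale and for both directions of a 10% shift. For a ratio of means with normal data this is about 62–83% at +10%, 80–98% at −10% and 88–99% at no shift. For log-ratios it is about 78–93% at +10% with a common CV, with a note that it is lower (about 66–87%) with equal SDs.
- Assess equivalence with a test that carries the uncertainty of the mean: either the paired contrasts (scan 2 − 1.3 × scan 1) and (scan 2 − 0.7 × scan 1), or log-ratios. Do not use 0.30 times the observed mean as if it were a fixed limit. Align section 7.1 with the choice.

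The cost is a reworded paragraph and a slightly different test statistic, with no extra patients, scans or staff. The downside is a less favourable stated power.
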